### Blinding

Research assistants will be blind to treatment allocation. To maintain blinding, all participants will be reminded not to discuss treatment with the research assistant at the follow-up assessment. When unblinding does occur, every effort will be made for future interviews with the participant to be conducted by a researcher who is still blind to treatment allocation. Success of the blind will be assessed by recording the RA’s judgement of treatment allocation for each participant at 4 months, 8 months and 12 months follow-up.

### Data management

The RPMS is used to manage all outcome data. The RPMS includes an electronic CRF (eCRF). The research assistants record participant-level data on an eCRF. These data are subsequently entered into the eCRF section of the RPMS. Self-report data are entered directly by the participant. The RPMS includes range restrictions to minimise data entry errors. The RPMS is accessed using a secure website and is stored on a secure server. It is designed to maintain the privacy and confidentiality of participant information and to ensure the integrity of the data. Access to RPMS is restricted to study personnel and the level of access is dependent on the person’s role. Data will be stored for a period of at least 25 years after the final publication arising from the study.

### Statistical methods

Primary analyses will be undertaken on an intention-to-treat basis. Mixed-model repeated measures (MMRM) analyses, including random intercepts to account for individual variability in baseline levels of social functioning, will be used to compare change in social functioning between the two treatment groups over the 12-month follow-up. MMRM is the analysis of choice because assumptions of traditional data analysis methods (eg, Analyis of Variance (ANOVA), logistic regression) may be violated, such as the assumption of homogeneity of regression across time points.^70^ Time (baseline, 4 months, 8 months and 12 months) will be the within-subjects factor and group (*Momentum* vs TAU) the between-subjects factor. Random intercepts account for individual differences in baseline levels of the outcome (eg, social functioning at the start of the study). However, individuals may also differ in how their outcomes change over time (eg, the rate or direction of improvement/decline in social functioning). Random slopes model this variability by allowing each participant to have their own trajectory (slope) over time. We will test whether including random slopes significantly improves model fit, but if the variance of slopes is negligible, a simpler model with only random intercepts will be adopted. MMRM will also be used to analyse change in the continuous secondary and exploratory outcomes over 12 months. Group differences in risk of transition to psychosis and vocational outcome will be tested using Fisher’s exact test, an alternative to the χ^2^ test more robust to small sample sizes.^71^ Time to transition to psychosis will be assessed by survival analysis (using either proportional hazard or accelerated life-time models).

Exploratory mechanisms of action (self-efficacy, social support and subjective well-being) analyses will be conducted using a multilevel structural equation modelling framework to assess mediation.^72^ Specifically, person-specific slopes representing change over time in the proposed mechanism-of-action variables (eg, self-efficacy) will be tested as mediators of the effect of treatment group (*Momentum* vs TAU) on social functioning.

Additional analyses will use multiple imputation to assess the robustness of the findings to the choice of method for handling missing data. Additional comparisons between treatment groups based on completer-only analyses will be conducted. Analyses will be undertaken in accordance with International Council for Harmonisation (ICH) 9 guidelines including a full analysis as well as per protocol set. The per protocol sample will be defined based on receiving a prespecified minimal exposure to the online intervention (ie, more than six logins over the 12-month intervention period).

The economic evaluation will comprise a cost-utility analysis, in addition to a cost-consequences analysis, comparing the incremental costs of the *Momentum* intervention (vs TAU) to a wide range of incremental study outcomes (eg, QALYs, social functioning, etc). Inclusion of the AQoL-8D questionnaire facilitates derivation of QALYs and enables a cost-utility analysis to be undertaken. A study-specific RUQ was adapted for this study from another RUQ frequently used in Australian mental health-related economic evaluations.^73^ The RUQ encompasses: community-based health service use; hospitalisations; accommodation services; medication and diagnostic tests; impacts on education and employment and other relevant services. Unit costs for resource use items will be sourced from nationally representative data sources, where available, with sensitivity analyses determining the impact of adopting alternative unit costs.^34^ The cost of delivering the *Momentum* platform will be estimated by microcosting data obtained from study-related financial records and intervention coordinators. Best practice within-trial economic evaluation methods will be adopted.^74^ The comparative cost-effectiveness of the *Momentum* platform (vs TAU) will be summarised using the incremental cost-effectiveness ratio metric (ie, cost per QALY gained). Statistical methods involving generalised linear models will be used to compare differences in costs and QALYs between groups. Bootstrapping will also be used to characterise uncertainty around the incremental cost-effectiveness ratio. A range of cost-effectiveness ratios outlined within the Productivity Commission Inquiry into Mental Health^75^ will be used to assess whether the *Momentum* platform is value for money. Briefly, a cost-effectiveness ratio of $A64 000/QALY will be used as the primary value-for-money criterion, with $A96 000/QALY deemed marginally cost-effective. If the *Momentum* platform is found to be effective, then a population-level budget impact analysis will be undertaken.

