### Sample size

Sample size was determined by power analysis using G*Power 3. The primary outcome is the difference in social functioning at 12 months. Our pilot study found a very large effect size (d=1.83, p<0.001) improvement in social functioning from baseline to 2-month follow-up.^39^ This contrasts with follow-up and treatment studies in UHR patients, where social functioning has not improved over time.^51^ Thus, we conservatively assume a medium treatment effect (Cohen’s *d*=0.45), for which a total sample of 180 participants is required to achieve 85% power (alpha=0.05) or 128 participants to achieve 80% power (Cohen’s *d*=0.5). The same applies to all continuous secondary outcome measures (eg, depression, anxiety, social anxiety, role functioning). A total of 220 young people will be recruited, allowing for an 18% attrition rate following randomisation. This compares favourably with the attrition rates in the *Momentum* pilot (7%).

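### The primary model carries baseline as a response and compares change, which is less precise than adjusting for baseline and is not the analysis that was powered

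*Protocol article*

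**What the plan says.** The Statistical methods section specifies a mixed model for repeated measures, "including random intercepts to account for individual variability in baseline levels of social functioning". It goes on: "Time (baseline, 4 months, 8 months and 12 months) will be the within-subjects factor and group" (Momentum versus TAU) the between-subjects factor. The stated purpose is to compare change in social functioning between the arms over the 12-month follow-up. Random slopes will be added if they improve fit. Neither a baseline covariate nor a common baseline mean for the two arms is mentioned. The same type of model is applied to the continuous secondary and exploratory outcomes.

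The Sample size section takes the difference in social functioning at 12 months as the quantity to be powered. It says "Sample size was determined by power analysis using G*Power 3" and "we conservatively assume a medium treatment effect (Cohen’s *d*=0.45"), for which "a total sample of 180 participants is required to achieve 85% power" at alpha 0.05. A second scenario, at d=0.5, gives "128 participants to achieve 80% power". Recruitment of 220 allows for 18% attrition. The section extends the calculation to the continuous secondary outcomes. The SD on which d is scaled and the correlation between baseline and follow-up are not given.

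The last section of the article says that the statistical analysis plan is limited to the protocol.

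**The concern.** When baseline is one of four response levels and each arm has its own mean at each level, the treatment effect at 12 months is the group-by-time contrast: the difference between arms in mean change from baseline. A random intercept models the correlation within a participant. It does not condition the treatment effect on the baseline score, although the article's description of it could be read that way. A chance imbalance at baseline is subtracted in full, when its regression weight would be the efficient amount to remove.

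Two things are at stake. The first is precision: baseline scores are collected on everyone, and the stated model does not make the best use of them. The second is the link to the sample size, because 85% power was calculated for a simple comparison at 12 months and the planned contrast has a different variance.

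**Working it through.** **Inputs.** From the Sample size section: d=0.45, alpha=0.05, 85% power, 180 analysed; d=0.5, 80% power, 128; 18% attrition, 220 recruited. From Trial design and setting: 1:1 allocation, so 90 per arm analysed. Assumed: rho, the baseline-to-12-month correlation, shown from 0.3 to 0.7; equal SDs at the two visits; d scaled on the 12-month SD; complete data on the 180.

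**Reproducing the plan's figures.** A two-sided two-sample t test at d=0.45 and 85% power needs 89.65, so 90 per arm or 180 in total; power at 90 per arm is 85.1%. At d=0.5 and 80% power it needs 63.8, so 64 per arm or 128. For attrition, 180/0.82 = 219.5, so 220. All three figures reproduce. A one-sided test would need only about 144, so the calculation is two-sided. The quantity powered is thus an unadjusted difference with variance 1 in units of SD squared.

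**Variance per participant, in the same units.**
- Change from baseline to 12 months: 1 + 1 − 2rho = 2(1−rho).
- 12-month score adjusted for baseline: 1 − rho².
- Ratio: 2(1−rho)/[(1−rho)(1+rho)] = 2/(1+rho), which exceeds 1 for every rho below 1.

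**Power with 90 per arm**, from the non-central t with effective d of 0.45/√(2(1−rho)) for change and 0.45/√(1−rho²) for the adjusted contrast:

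| rho | Variance ratio | Effective d, change | Power, change | Effective d, adjusted | Power, adjusted |
|---|---|---|---|---|---|
| 0.3 | 1.54 | 0.380 | 72% | 0.472 | 88% |
| 0.4 | 1.43 | 0.411 | 78% | 0.491 | 91% |
| 0.5 | 1.33 | 0.450 | 85% | 0.520 | 93% |
| 0.6 | 1.25 | 0.503 | 92% | 0.563 | 96% |
| 0.7 | 1.18 | 0.581 | 97% | 0.630 | 99% |

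The break-even for the change contrast is where 2(1−rho) = 1, that is rho = 0.5. Below that, the analysed total needed for 85% power is 252 at rho 0.3 and 216 at rho 0.4 (308 and 264 recruited at 18% attrition); the adjusted contrast needs 164 and 152. A simulation of 4,000 trials per value, with the change contrast tested under a random-intercept model, agrees: 71% against 88% at rho 0.3, 87% against 94% at 0.5, 97% against 99% at 0.7.

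**Other readings of the contrast.** The article does not name one.
- *Change averaged over the three follow-ups*, with compound symmetry and a constant effect of 0.45. The variance is (1+2rho)/3 + 1 − 2rho = (4/3)(1−rho), so the break-even is rho = 0.25. Power is 87% at rho 0.3 and 92% at 0.4. The adjusted variance is (1+2rho)/3 − rho² = (1−rho)(1+3rho)/3, a ratio of 4/(1+3rho), again above 1 for every rho below 1.
- *A 3-df group-by-time test*, with an effect growing linearly to 0.45. Power is 60% at rho 0.3, 76% at 0.5 and 86% at 0.6.

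**The case against.** A reader might infer that the trial has less than its stated 85% power. The document does not support that, for three reasons. First, rho is not given, and at 0.5 or above the stated model meets or exceeds 85%. Second, the SD behind d is not given. The effect size was argued down from a pilot improvement from baseline, so d may be scaled on the SD of change; the change contrast then has 85% power by construction. The reference to a difference at 12 months points the other way but does not settle it. Third, the contrast is not named. The outcome is described as social functioning over 12 months, and averaging change over the follow-ups moves the break-even down to 0.25, although a 3-df interaction test would lower power.

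A reader might also infer bias, or that baseline is ignored. Neither follows. Randomisation keeps the comparison of change unbiased, and subtracting baseline does account for it, only inefficiently.

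Finally, free group means at baseline are the natural reading of the factor list, not something the article says outright. A model with baseline as a response and a common baseline mean would fit the same sentence, and the full protocol, which is not shown, may say more.

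All of this limits the power claim and the certainty of the reading. It does not remove the precision argument: if the group means are free at baseline, adjustment is more precise under either scaling of d and for any rho below 1.

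**Conclusion.** The point holds as a matter of efficiency and of a mismatch with the sample size calculation. As naturally read, the stated model gives a 12-month contrast with 25% to 54% more variance than a baseline-adjusted one for rho between 0.6 and 0.3, and it is not the t test from which 180 was derived. A shortfall against 85% arises only if rho is below 0.5, d is scaled on the 12-month SD and the contrast is 12 months minus baseline. With a baseline-adjusted 12-month contrast and d on that scale, power is at least 85% whatever rho is. This is a free improvement that should be made, not a correction of bias or of the sample size arithmetic.

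**What to change.** Replace the description of the primary model with one of these:

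- Take the 4-, 8- and 12-month scores as responses, with group, visit and group-by-visit as effects and with baseline Global Functioning: Social and its interaction with visit as covariates.
- Keep baseline as a response, but constrain both arms to a common baseline mean and use an unstructured covariance. The data then set the weight given to baseline at each visit, which a random intercept alone would not allow.

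In either case name the group difference at 12 months as the primary contrast, so that it matches the Sample size section, and say there which SD d is scaled on. Apply the same model to the continuous secondary outcomes, to which the power statement is extended.

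The cost is a change of wording, made before any unblinded analysis. No new data are needed: the Participant timeline section has participants randomised after baseline measures are complete.

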### Trial design and setting

The study design is a prospective, parallel-group, rater-masked, superiority RCT with a 1:1 allocation ratio. Approximately 220 participants at UHR for psychosis will be allocated to either TAU or TAU + *Momentum*.

The trial includes a 4-year recruitment period, commencing in November 2019, and a 12-month treatment phase, with the study being completed within 5 years (December 2024). The design comprises four monthly assessment points across 12 months. The protocol development addressed all aspects of Good Clinical Practice,^43^ Consolidated Standards of Reporting Trials EHEALTH criteria^44^ and Standard Protocol Items: Recommendations for Interventional Trials guidelines.^45^

Participant recruitment commenced in October 2019 at services in the North-Western Melbourne (Victoria, Australia) catchment. Specifically, recruitment took place through the Personal Assessment and Crisis Evaluation (PACE) programme, a part of the Orygen Specialist Program and headspace centres led by Orygen (in the Melbourne suburbs of Sunshine and Glenroy). These services support young people who may be at risk of developing psychosis.^46 47^ Orygen is the world’s largest research and knowledge translation organisation focused on early intervention in mental ill-health in young people.

Orygen Digital, the digital mental health division of Orygen and Centre for Youth Mental Health at The University of Melbourne, designs, delivers and evaluates evidence-based digital services for youth mental health. In April 2020, Orygen Digital commenced implementation of the MOST platform across all Victorian youth mental health services both as part of the Victorian State Government’s response to the COVID-19 pandemic and in response to the recommendations of the Royal Commission into Victoria’s Mental Health System.^48^ Due to the overlap between study and implementation sites, participant recruitment from Victorian sites ceased in October 2020. Instead, satellite recruitment sites were established at two services within the South-Eastern Sydney Local Health District (Bondi Junction Community Mental Health Centre and headspace Bondi Junction) and at headspace services in the Illawarra region, New South Wales (NSW), operated by Grand Pacific Health (Wollongong, Nowra).

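### The primary model's covariance is left to an undefined random-slope test; the harm at month 12 is modest under a formal test, and an unstructured covariance avoids it at negligible cost

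*Protocol article*

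**What the plan says.** Under Statistical methods, the protocol article specifies "Mixed-model repeated measures (MMRM) analyses, including random intercepts to account for individual variability in baseline levels of social functioning". The mean structure is categorical: "Time (baseline, 4 months, 8 months and 12 months) will be the within-subjects factor", with group as the between-subjects factor. Random slopes are then conditional: "We will test whether including random slopes significantly improves model fit, but if the variance of slopes is negligible, a simpler model" (intercepts alone) is to be used instead. The section names no test, no significance level, no threshold for a negligible variance and no residual covariance. The same approach is used for the continuous secondary and exploratory outcomes.

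The additional analyses in that section (multiple imputation, completers, per protocol) deal with missing data and adherence, not covariance. The section Protocol and statistical analysis plan says that the analysis plan does not extend beyond the protocol.

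The primary contrast is described in two ways. The Sample size section takes the difference at 12 months. The Outcomes section defines the outcome over the 12 months.

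**The concern.** In a repeated-measures model the assumed covariance sets the standard error of the treatment contrast. A random intercept with independent, constant-variance residuals makes any two visits equally correlated, however far apart. Correlations that fall with time, or a baseline that relates less closely to follow-up than the follow-up visits do to each other, break that assumption. The standard error of change from baseline is then too small. If baseline is less variable than follow-up, it can be too large.

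The slope step is meant to catch this, but it has two weaknesses. It joins two criteria, significant improvement in fit and negligible variance, and defines neither, so the analyst could reach either model from the same data. And a linear slope repairs only some departures. At stake are the calibration of the primary p-value and freedom from a data-dependent choice that four fixed visits do not require.

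**Working it through.** **Inputs from the protocol.** Four visits; two groups, 1:1; alpha 0.05; d = 0.45; "a total sample of 180 participants is required to achieve 85% power (alpha=0.05) or 128 participants to achieve 80% power" (the second figure is for d = 0.5); 220 recruited with 18% attrition. The article gives no standard deviation or correlation for the scale, so every covariance below is an assumption.

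**The plan's own figures.** A two-sided two-sample t-test (noncentral t) gives power 0.851 at N = 180 with d = 0.45, and 0.801 at N = 128 with d = 0.5. 180/0.82 = 219.5, so 220. The sample size reproduces and is not in question.

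**Formula.** Let G be the true 4×4 covariance, S the best-fitting covariance of the assumed form, and c the contrast. The large-sample two-sided error is 2·[1 − Φ(1.96·k)], with k = √(c'Sc / c'Gc). For the random intercept, S has the average variance and the average covariance of G. For intercept plus slope, S minimises log|S| + tr(S⁻¹G).

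**Random intercept, AR(1) with correlation 0.7, month 12 minus baseline.** Average correlation = (3×0.7 + 2×0.49 + 0.343)/6 = 0.5705. Assumed variance 2(1 − 0.5705) = 0.859; true variance 2(1 − 0.343) = 1.314. k = √(0.859/1.314) = 0.8085, so the error is 11.3%.

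**Random intercept, mean follow-up minus baseline, correlation 0.4 with baseline and 0.7 among follow-ups.** Average correlation 0.55. Assumed variance (1 − 0.55)(1 + 1/3) = 0.60; true variance 1 + (3 + 6×0.7)/9 − 2×0.4 = 1.00. k = 0.7746, so the error is 12.9%.

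**Large-sample type I error (%), by the same method**

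| Assumed pattern | Month 12: intercept only | Month 12: slopes kept | Average: intercept only | Average: slopes kept |
|---|---|---|---|---|
| AR(1) 0.5 | 9.2 | 4.3 | 7.3 | 4.8 |
| AR(1) 0.7 | 11.3 | 4.3 | 8.3 | 4.8 |
| AR(1) 0.85 | 12.9 | 4.4 | 9.0 | 4.8 |
| Mild decay 0.65, 0.60, 0.55 | 7.0 | 4.8 | 6.0 | 5.0 |
| Baseline 0.5, follow-ups 0.6 | 6.3 | 5.4 | 7.6 | 7.1 |
| Baseline 0.4, follow-ups 0.7 | 9.0 | 6.0 | 12.9 | 11.0 |
| Baseline 0.3, follow-ups 0.8 | 11.6 | 6.5 | 17.7 | 14.3 |
| Baseline SD 0.7 of follow-up, correlation 0.5 | 3.7 | 3.3 | 2.5 | 2.3 |
| Baseline SD 0.5 of follow-up, correlation 0.5 | 3.4 | 2.5 | 2.0 | 1.7 |

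**The two-step rule, read as a likelihood-ratio test at 0.05** (simulation, 90 per arm, complete data, 1,500 runs, Monte Carlo SE about 0.6 points). Slopes are selected in 98-100% of trials under strong decay, about 93% with baseline 0.4 and follow-ups 0.7, about 60% under mild decay and 41% with a small true slope variance. The month-12 error of the rule is about 4-6% under decaying correlation. It falls to 3.0% with baseline SD 0.6 of follow-up and equal correlations. An unstructured covariance gives about 4-6.6% across all patterns, within about three Monte Carlo SEs of 5%.

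**With 18% dropout** (110 per arm, 500 runs, SE about 1 point), the month-12 errors for intercept only / rule / unstructured are:
- AR(1) 0.7: 12.2 / 4.8 / 5.2%
- baseline 0.4, follow-ups 0.7: 8.6 / 4.2 / 4.2%
- mild decay: 6.0 / 4.4 / 3.8%

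**Power effect of conservatism.** A true size of 2.9% corresponds to z = 2.183, so the standard error is 2.183/1.96 = 1.11 times too large. Power becomes Φ(1.96 + 1.036 − 2.183) = Φ(0.813), about 79% instead of 85%. A size of 3.8% (z = 2.075) gives Φ(0.921), about 82%.

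**Cost of the unstructured model when compound symmetry is true.** Month-12 power, unstructured against the rule: 0.743 v 0.750 (correlation 0.6) and 0.792 v 0.791 (correlation 0.4) with complete data; 0.878 v 0.874 with dropout. For the 3-df group-by-time test: 0.634 v 0.645 and 0.665 v 0.675.

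**The case against.** The strongest reply is that the rule largely corrects itself. The large errors belong to the random-intercept model, and where decay is strong a formal slope test almost never leaves that model in place. With the plan's own 18% dropout, the rule and the unstructured model cannot be told apart at month 12. This stands. A reader might infer that the primary analysis as planned more than doubles its type I error; the calculations do not support that for a formal 5% test.

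A reader might also infer a power loss from 85% to about 80%. That needs a baseline SD of roughly 0.6 of the follow-up SD, and nothing in the article shows such a restriction; the eligibility criteria set no social-functioning threshold.

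Nor is the choice post hoc. The candidate models are named in advance, and the choice concerns a variance, not the treatment estimate. What is missing is the decision criterion.

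Finally, a condensed article may leave the residual structure and degrees-of-freedom method to a fuller document, and equal correlation follows only if none is added. That is fair, and the omission is not the point. The point is what the article does fix: a random-intercept default with a data-driven slope step.

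Two things remain. The modest result assumes a formal test that the article does not define; if slopes are dropped by judgement, the intercept-only errors apply. And for a contrast averaged over follow-up, keeping slopes does not restore calibration when baseline behaves differently.

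**Conclusion.** The point holds as a modest, avoidable weakness in the primary analysis. At month 12 the error is about 7-13% if slopes are dropped while correlations decay or baseline is less correlated with follow-up (6.3% in the mildest case tabulated), and about 2.5-6.5% if slopes are kept. For the average over follow-up with slopes kept, it is about 2-14% when baseline differs from follow-up in correlation or spread, and close to 5% under simple decay.

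All of these figures rest on assumed covariances. The averaged-contrast results are large-sample values only, and Kenward-Roger degrees of freedom were not simulated. The documents cannot show which pattern applies, so they do not support a claim that the trial's test is in fact miscalibrated, or that such patterns are common for this scale. They do show that the plan depends on the pattern where it need not.

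**What to change.** Before any unblinded analysis, prespecify the primary MMRM with categorical visit, group, group-by-visit and an unstructured within-person covariance, using a small-sample degrees-of-freedom method such as Kenward-Roger. State an ordered fallback list of covariance structures, to be used only for non-convergence. Remove the random-slope test from the primary analysis. Name one primary contrast, month 12 or the average over follow-up, because the exposure differs between them.

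The cost is a few sentences in the analysis section and about 0-1 power point if compound symmetry is true. A 4×4 covariance has 10 parameters, which about 180-220 participants can support. The sample size does not change.
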